### Sampling frame

A complete list of confirmed cases of hypertension attending the two NCD clinics and residing in either Nakaseke Town Council, Nakeseke Subcounty, or Kasangombe generated by the data manager.

### Intervention

The multi-component intervention will be centered on monthly pro-active household visits by trained CHWs for a period of 1 year.

It will consist of the following:Blood pressure and sugar monitoring. CHWs will be trained in measuring blood pressure using a digital blood pressure machineBMI monitoringCardiovascular disease risk assessmentUse of checklists to guide monitoring and referral to the clinics. Checklists will be filled in and handed over to the project staff for review at the end of every weekHealthy lifestyle counseling and education. CHWs will be trained in a curriculum regarding home health education and strategies regarding behavioral change communication. The education will be provided to participants and all the family members during the home visitFollow-up during home visits to ensure that patients received all prescribed medications and to encourage them to adhere to themProviding patient-education using PocketDoktor™ booklets, an established education tool among hypertensive patients in rural settings [22]

During home visits, CHWs will remind patients of follow-up visits and encourage clinic attendance.

### Usual care

This involves monthly to three monthly patient visits to any of the two existing NCD clinics in Nakaseke. Clinics use the adopted tools for implementing WHO PEN (Package of Essential Non-Communicable Diseases Interventions) in the management of patients [23]. Routine clinic activities include taking of vital signs, group counseling, and review by the clinicians, medication prescription, and medical investigations as well as drug prescription and administration. All the participants will continue with the usual care. Implementing the CHW approach will not require alteration to usual pathways including use of any medication, for both trial arms. There are no restrictions regarding concomitant care during trial.

### Discontinuation

Participants who chose to discontinue from the intervention or the protocol will not have individually data collected through the fieldworkers. Analysis will be done through intention to treat.

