**Methods:**

We will conduct a stepped-wedge cluster randomized controlled trial study of 869 adult patients with hypertension attending two NCD clinics to test the effectiveness, acceptability, and fidelity of a CHW-led intervention. The multi-component intervention will be centered on monthly household visits by trained CHWs for a period of 1 year, consisting of the following: (1) blood pressure and sugar monitoring, (2) BMI monitoring, (3) cardiovascular disease risk assessment, (4) using checklists to guide monitoring and referral to clinics, and (5) healthy lifestyle counseling and education. During home visits, CHWs will remind patients of follow-up visits. We will measure blood pressure at baseline and 3-monthly for the entire cohort. We will conduct individual-level mixed effects analyses of study data, adjusting for time and clustering by patient and community.

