### Study design

The study will employ a closed cohort, superiority stepped wedge cluster randomized design. There will be a sequential crossover of clusters from the control to the intervention arms and the order of the cross over will be randomly determined (Fig. 1). This study will be conducted in 21 clusters within Nakaseke district. Each cluster will consist of 4–5 villages (Table 1). Participant recruitment will occur before randomization. At the beginning of the study period, we will collect baseline demographic data from each of the participants. All the villages within the study will eventually receive the intervention, thereby improving equity and acceptability. To minimize contamination, we will ensure that clusters are well separated to minimize social contact between participants in the intervention and control arms. Since all clusters will be observed under both the intervention and control arm, we anticipate that imbalances are less likely to occur. To further address the issue of contamination, individuals within the same cluster will be randomized to receive the intervention at the same time. Also, since the study will be conducted in a rural population, we expect adjacent neighborhoods to be far apart from each other, and this could additionally reduce the rates of contamination within the study area. In addition, CHW activities are directed to individuals at the level of the home and not large community groups or gatherings. This should decrease exposure of non-enrolled patients from outside randomized clusters to the interventions. We plan to rollout the intervention in two clusters per month and one cluster in the final month (Fig. 2).

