### Recruitment, enrollment, and retention

Research assistants, who will obtain informed consent and collect the baseline and three-monthly data, will enroll study participants from the NCD clinics. Participants will be contacted by the CHWs, prior to the intervention rollout to schedule an initial home visit. The baseline assessment will be conducted following the WHO’s STEPwise approach to surveillance, a standard method for analyzing risk factors for NCDs, such as data collection on risk factors using the questionnaire and bio-physical measurements [18].

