### Data analysis

Patient characteristics will be summarized using proportions for categorical variables. Means (standard deviations) and medians (interquartile ranges) will be used for continuous variables by exposure period (intervention and control periods). The chi-square and Fisher’s exact test will be used to test for differences in participant characteristics for categorical variables by exposure period status. The one-way ANOVA will be used to compare means between the two periods for normally distributed continuous variables, and Kruskal-Wallis test will be used for non-normally distributed continuous variables.

We will follow the intention-to-treat principle, and clusters will be analyzed according to their randomized crossover time irrespective of whether crossover was achieved at the desired time. Mixed effects logistic regression models will be used to assess the impact of the intervention on the primary outcome. These models will be fitted with time treated as a fixed effect at each step. Also, since calendar time is hypothesized to be associated with both the exposure (intervention) to the intervention and the outcome, we will adjust for this as a potential confounder in the final analysis. To account for dependence between individual measurements, an additional random effect for individuals in the study will be added into the model. The estimated intra-cluster correlation and time effect from the fitted model will be reported for use in the design of future trials and to allow appreciation of any underlying confounding effects of calendar time. The period a particular cluster has been exposed to the intervention will be accounted for in the final model as an effect modifier. For the secondary binary outcomes, we intend to employ the same methods as above for analysis. However, linear mixed-effects models accounting for temporal trends will be used to assess the intervention impact on the different continuous secondary outcomes. In the case of missing data, we will capitalize on multiple imputation techniques to handle the issue of missing data in this study.

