### Data safety and management

Data will be managed using Research Electronic Data Capture (REDCap; Vanderbilt University, Nashville, USA). This will be collected by well-trained research assistants using secure password-protected tablet computers with Research Electronic Data Capture (REDCap; Vanderbilt University, Nashville, USA). All paper case report forms or source documents will be filed and stored in lockable designated cabinets and rooms. To protect participants’ confidentiality all data will be identified by anonymized study numbers. Only authorized study staff, e.g., those that collect data in the clinics will have the possibility to link the anonymized information to other participant identifiers. The data will be stored in password-protected database with no participants’ identifying information. Designated study team members will have exclusive rights to the database. Database access for other members of the study team will be determined by their responsibilities on the study, e.g., data entry, query resolution, and data monitoring. For this study, we will capitalize on single data entry. Majority of the range and consistency checks will be inbuilt into the REDCap software. In addition, the study data manager will run routine consistency checks on the study data using STATA version 15 software. At publication of the findings of this study, no identifying information will be used.

ACCESS will serve as the study coordinating center and be responsible for training, regulatory oversight, data management, and community engagement. The coordinating center will be responsible for daily operations including data collection, the training of field workers and community health workers, and participant enrollment. The study team at the coordinating center will be comprised of the project manager, the study biostatistician, and the study physician. The trial steering committee will meet every 2 weeks. This committee is comprised of the principal investigator, project manager, co-investigators, and study statistician. This team will review enrolment and study endpoints. In addition, a stakeholder and public group will be part of this study. This will comprise a community advisory board of community leaders, health works, and Ministry of Health officials. The community advisory board will meet quarterly. The PI will present the study updates as well as obtain input from the community advisory board regarding community concerns.

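### The discontinuation rule ends outcome collection for people who only stop the intervention, which conflicts with whole-cohort follow-up and removes readings the intention-to-treat analysis needs

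*Protocol article*

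**What the plan says.** All references are to the protocol article.

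- **Discontinuation:** "Participants who chose to discontinue from the intervention or the protocol will not have individually data collected through the fieldworkers". The next sentence reads: "Analysis will be done through intention to treat".
- **Data analysis:** "We will follow the intention-to-treat principle, and clusters will be analyzed according to their randomized crossover time", whether or not crossover took place on schedule. The same section plans a random effect for individuals and multiple imputation for missing data, without stating the imputation assumption.
- **Abstract, Methods:** "We will measure blood pressure at baseline and 3-monthly for the entire cohort".
- **Recruitment, enrollment, and retention:** the outcome data are assigned to "Research assistants, who will obtain informed consent and collect the baseline and three-monthly data".
- **Data safety and management:** the coordinating center's duties include "the training of field workers and community health workers", which names the two groups separately.
- **Study design:** "There will be a sequential crossover of clusters from the control to the intervention arms". The cohort is closed.

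**The concern.** Stopping an intervention and withdrawing from data collection are different events. A participant may decline further home visits and still be willing to have blood pressure measured every three months. The discontinuation rule merges the two, so a refusal of visits ends the outcome record as well.

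Intention to treat compares people as randomized, whether or not they kept taking up the intervention, so it needs the outcomes of those who stopped. In this design a participant can stop CHW visits only once the cluster has crossed over, so readings lost for that reason belong to intervention periods. If people who stop visits also lose some of the benefit, the remaining intervention-period data come increasingly from those who kept accepting visits. The planned modelling of time since exposure as an effect modifier is open to the same problem, because refusals can accumulate as exposure lengthens.

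The primary outcome is affected, and readings that were never taken cannot be recovered at analysis.

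**Working it through.** **1. Does the rule reach the outcome measurements?** The harmless reading is that fieldworkers means CHWs, so that only data from CHW visits stop. Data safety and management lists field workers and CHWs as two groups, which counts against that reading. Fieldworkers is never defined, and the three-monthly data are assigned to research assistants, so the two terms cannot be shown to be identical either. No section names another source of blood pressure after discontinuation. Taken literally, the sentence ends study measurement for people who stop only the intervention, and that does not fit with measuring the entire cohort.

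**2. In which periods do the lost readings fall?**
- Stopping the intervention: the cluster must already have crossed over, and it does not cross back. Later missed readings are intervention-period readings.
- Leaving the protocol: possible before or after crossover, so control-period readings can be lost too.

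Loss is therefore relatively greater under intervention, but not confined to it.

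**3. What can imputation use?** It can use each person's readings before discontinuation and the readings of people who continued. Under the rule it has no reading from anyone after discontinuation. A standard missing-at-random imputation would give discontinuers the intervention effect seen in similar continuers.

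**4. Size.** The article gives no discontinuation rate to reproduce. The only figure taken from it is the 6 mmHg target (Sample size determination). The stated sample size of 869 does not enter the calculation. It cannot be checked in any case, since no standard deviation or intra-cluster correlation is given.

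Assumptions:
- the effect in continuers is 6 mmHg;
- d, the share of exposed participants who discontinue, is 5%, 10% or 20%;
- e, the effect that discontinuers keep, is 0 (none) or 3 mmHg (half).

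Effect if outcomes are still collected: (1 − d) × 6 + d × e.
Estimate if discontinuers are treated as continuers: 6.
Overstatement: 6 − [(1 − d) × 6 + d × e] = d × (6 − e).

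| d | e (mmHg) | Effect with outcomes collected (mmHg) | Overstatement (mmHg) | Share of 6 mmHg |
|---|---|---|---|---|
| 5% | 0 | 0.95 × 6 = 5.70 | 0.30 | 5% |
| 10% | 0 | 0.90 × 6 = 5.40 | 0.60 | 10% |
| 20% | 0 | 0.80 × 6 = 4.80 | 1.20 | 20% |
| 5% | 3 | 5.70 + 0.15 = 5.85 | 0.15 | 2.5% |
| 10% | 3 | 5.40 + 0.30 = 5.70 | 0.30 | 5% |
| 20% | 3 | 4.80 + 0.60 = 5.40 | 0.60 | 10% |

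This is a first approximation. It counts a discontinuer as lost for all of that person's intervention-period readings, so people who stop late contribute less than the table shows.

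**The case against.** **Ambiguous wording in a condensed article.** Fieldworkers is undefined, a full protocol exists, and usual-care clinic visits with vital signs continue for everyone. This stands in part: the full protocol may be clearer. But the article states a rule here and does not merely omit a detail. It nowhere says that clinic readings would serve as outcomes, and staff who follow the sentence literally would stop measuring.

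**Intention to treat can be run with missing data.** This stands. Clusters are still analysed by randomized crossover time, and imputation is an accepted tool. The fault is that the rule creates missingness that need not occur, not that an intention-to-treat analysis becomes formally impossible.

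**Stronger readings that the document does not support.**
- A reader might infer that data go missing in intervention periods only. The rule also covers leaving the protocol, which can happen in control periods. CHWs also contact participants before rollout, so a refusal could come shortly before crossover.
- A reader might call the result a per-protocol comparison under an intention-to-treat label. Readings taken before discontinuation stay in, as do people who adhere poorly without formally discontinuing.
- A reader might multiply the share discontinuing by an assumed raw gap in systolic pressure between discontinuers and continuers. With 20% and 10 mmHg this gives 2.0 mmHg, or 33% of the target. In a closed cohort with an individual random effect, each person's earlier readings absorb part of any stable difference. If the gap is instead lost benefit, it cannot exceed 6 mmHg unless stopping visits does harm. The expression d × (6 − e) is the better guide.

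**Conclusion.** The point holds. The discontinuation sentence conflicts with three-monthly measurement of the entire cohort and removes outcomes that the intention-to-treat analysis needs. The missingness is avoidable, probably informative and relatively greater under intervention.

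For assumed discontinuation of 5–20%, treating discontinuers as continuers would overstate the effect by 0.15–1.2 mmHg, or 2.5–20% of the 6 mmHg target. That range rests on assumed discontinuation rates and residual effects, and on an analysis that carries the continuers' effect over to discontinuers. A bias in favour of the intervention is probable, because those who stop visits are likely to lose benefit, but it is not certain: people may stop for reasons unrelated to blood pressure, or because they are doing well.

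**What to change.** Reword the Discontinuation section to separate two cases:

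1. A participant who stops CHW visits remains in follow-up, and the research assistants' three-monthly outcome measurements continue.
2. Only withdrawal of consent to data collection ends those measurements.

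Replace fieldworkers with the role that is meant, and bring the consent wording into line.

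The cost is small. Three-monthly measurement of the whole cohort is already planned, so no new procedure is added. The article does not say where those readings are taken, so the effort of reaching people who have declined visits cannot be judged exactly. The downside is some follow-up contact with people who have declined CHW visits; they keep the right to withdraw from data collection. The change concerns data collection only and leaves clinical care as it is.

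A sensitivity analysis allowing for data missing not at random would be a useful addition, but it is optional and can be left to the statistical analysis plan.

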### Procedures

Research assistants will collect sociodemographic data, exposure history and co-morbidities.

i. An average of three blood pressure measurements taken in a seating position after 10 minutes of rest according to recent guidelines [24] using an automatic Omron M4-1 sphygmomanometer. The blood pressure will be classified according to National Institute of Health (NIH) guidelines

ii. Height using a portable stadiometer to the nearest decimal point in centimeters

iii. Weight with digital Seca mechanical scales to the nearest kilogram. We will calculate for the BMI from the formula BMI = (𝑊𝑒𝑖𝑔ℎ𝑡 in 𝑘𝑔) ÷ (𝐻𝑒𝑖𝑔ℎ𝑡 in 𝑚) Using the NIH guidelines, the BMI will be classified as underweight (< 18.5), normal (18.5–24.9), overweight (25.0–29.9), and obesity (30.0–34.9) [25]

iv. Waist circumference and hip circumference will be obtained using a tape measure to the nearest decimal point in cm. This will be used to obtain the waist to hip ratio

v. Random and fasting blood sugars (RBS/FBS) will be measured using capillary blood

### Data collection and management

We will collect the study data on secure password-protected tablet computers with Research Electronic Data Capture (REDCap; Vanderbilt University, Nashville, USA). The data manager will crosscheck for completeness and correctness. It will then be exported to STATA 15 for analysis. We will conduct monthly checks of the data to assess completeness and outliers by the data manager and PI.

### Data analysis

Patient characteristics will be summarized using proportions for categorical variables. Means (standard deviations) and medians (interquartile ranges) will be used for continuous variables by exposure period (intervention and control periods). The chi-square and Fisher’s exact test will be used to test for differences in participant characteristics for categorical variables by exposure period status. The one-way ANOVA will be used to compare means between the two periods for normally distributed continuous variables, and Kruskal-Wallis test will be used for non-normally distributed continuous variables.

We will follow the intention-to-treat principle, and clusters will be analyzed according to their randomized crossover time irrespective of whether crossover was achieved at the desired time. Mixed effects logistic regression models will be used to assess the impact of the intervention on the primary outcome. These models will be fitted with time treated as a fixed effect at each step. Also, since calendar time is hypothesized to be associated with both the exposure (intervention) to the intervention and the outcome, we will adjust for this as a potential confounder in the final analysis. To account for dependence between individual measurements, an additional random effect for individuals in the study will be added into the model. The estimated intra-cluster correlation and time effect from the fitted model will be reported for use in the design of future trials and to allow appreciation of any underlying confounding effects of calendar time. The period a particular cluster has been exposed to the intervention will be accounted for in the final model as an effect modifier. For the secondary binary outcomes, we intend to employ the same methods as above for analysis. However, linear mixed-effects models accounting for temporal trends will be used to assess the intervention impact on the different continuous secondary outcomes. In the case of missing data, we will capitalize on multiple imputation techniques to handle the issue of missing data in this study.

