### Primary outcome

Decrease in the average systolic pressure between the intervention and control arms.

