### Sample size determination

The primary outcome will be a change in systolic blood pressure between the intervention and control group. To compute the required sample size for the step wedge design, we first computed the required sample size if we were to implement an individual randomized trial. By conservative estimates, we estimate a 6-mmHg difference in systolic blood pressure between the intervention and control group [20, 21]. Accounting for the stepped-wedge design and constant cluster sizes (40) within the sample, with a fixed number of clusters (*n* = 21) and a power of 90%, at 0.05% level of significance, a sample size of 869 will power the study to detect an absolute minimally important clinical difference (MCID) of 6 mmHg in the mean systolic blood pressure between the intervention and control arms. We intend to roll out the intervention within two clusters each month and within one cluster during the final month.

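### The primary outcome is mean systolic pressure in mmHg, but the named primary analysis is mixed-effects logistic regression, which cannot estimate or test the 6 mmHg difference the trial is sized for

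*Protocol article*

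**What the plan says.** The Primary outcome section gives a continuous quantity: "Decrease in the average systolic pressure between the intervention and control arms". Sample size determination repeats it ("The primary outcome will be a change in systolic blood pressure between the intervention and control group") and sets the trial size "to detect an absolute minimally important clinical difference (MCID) of 6 mmHg in the mean systolic blood pressure between the intervention and control arms".

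The Data analysis section names the model: "Mixed effects logistic regression models will be used to assess the impact of the intervention on the primary outcome". It goes on to apply that approach to the binary secondary outcomes, and then, as a contrast, says that "linear mixed-effects models accounting for temporal trends will be used to assess the intervention impact on the different continuous secondary outcomes".

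Under Secondary outcomes, blood pressure control (below 140/90) appears as a binary endpoint and is secondary only. The abstract speaks of individual-level mixed effects analyses without saying whether they are linear or logistic.

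**The concern.** A mixed-effects logistic model is for a yes/no response. To apply it to systolic pressure, someone must first choose a cut-point, and the article gives none for the primary outcome. Three things are at stake.

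- **The question changes.** The primary result would be an odds ratio for being below some threshold. With the obvious cut of 140 mmHg, it would be a near relative of the secondary control endpoint. It would not be identical to it, because that endpoint also involves diastolic pressure.
- **The choice is left open.** The analyst must give up either the declared outcome or the declared model. If that is settled after data are seen, a mmHg result and an odds ratio are both available to pick from.
- **Information is lost.** Dichotomising lowers power for the same underlying shift. The intra-cluster correlation that the article promises to report for future trials would also not be on the mmHg scale that a trial sized like this one needs.

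**Working it through.** **1. The passages side by side (Protocol article)**

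| Section | Treats the primary outcome as |
|---|---|
| Primary outcome | continuous: average systolic pressure |
| Sample size determination | continuous: 6 mmHg in the mean |
| Secondary outcomes | the binary blood pressure endpoint is secondary |
| Data analysis | binary: logistic model, grouped with the binary secondary outcomes; linear models only for continuous secondary outcomes |

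Replacing the single word for the model would not repair the paragraph. The next sentence, which carries the method over to binary secondary outcomes, would then point to a linear model. The paragraph is written throughout as though the primary outcome were binary.

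**2. The plan's own figure**

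The total of 869 cannot be confirmed or refuted, because the article gives no SD, intra-cluster correlation or within-person correlation. For scale, with individual randomisation, N = 4·SD²·(z₁₋α/₂ + z₀.₉₀)²/6². This equals 869 at SD ≈ 27.3 for a two-sided α of 0.05, or at SD ≈ 18.6 if the printed 0.05% is taken literally as 0.0005. Either way the calculation is for a mean in mmHg, so the trial is sized for a linear analysis.

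**3. Loss from dichotomising: general formula**

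Assumptions, none given in the article: normal outcome, independent observations, two-sided 5%, proportion controlled p of 0.5 or 0.3.

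- Relative efficiency = φ(z_p)² / [p(1−p)].
  - p = 0.5: 0.3989²/0.25 = 0.637
  - p = 0.3: 0.3477²/0.21 = 0.576
- 90% power at two-sided 5% corresponds to a standardised effect of 1.960 + 1.282 = 3.2415.
- Power after dichotomising = Φ(3.2415·√efficiency − 1.960).
  - p = 0.5: Φ(2.586 − 1.960) = 0.734
  - p = 0.3: Φ(2.459 − 1.960) = 0.691

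**4. Loss from dichotomising: explicit cut at 140 mmHg**

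Assumptions: control mean 145–155 mmHg, SD 15–25 mmHg, individual randomisation, two-sided 5%.

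Worked case, mean 150 and SD 20:

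- Proportion below 140 in controls: Φ((140 − 150)/20) = Φ(−0.5) = 0.309.
- After a 6 mmHg fall: Φ((140 − 144)/20) = Φ(−0.2) = 0.421.
- Odds ratio: (0.421/0.579)/(0.309/0.691) ≈ 1.63.
- N for 90% power: 468 on the mean and 770 on the proportion, a ratio of 1.65.
- Power on the proportion with N = 468: 71%.

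Over the whole grid:

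| Quantity | Range |
|---|---|
| Odds ratio equivalent to 6 mmHg | 1.47–2.00 |
| Binary N ÷ continuous N | 1.58–2.01 |
| Binary power at the N giving 90% on the mean | 63–73% |

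The same 6 mmHg maps to different odds ratios depending on the mean and SD. An odds ratio alone therefore cannot be turned back into the mmHg difference for which the trial was sized.

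**The case against.** The strongest reply is that an unseen analysis plan or full protocol may hold the right model, and that the abstract's wording is compatible with a linear one. That would answer a complaint about missing detail. Here the article does name a model, and it conflicts with the outcome declared a few sections earlier.

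A second reply is that the stated aim, in the abstract and the Discussion, is blood pressure control, so a binary primary outcome may have been intended. This may explain where the wording came from. However, the Primary outcome and Sample size determination sections both commit to a mean, so a linear model is the natural repair. The investigators should confirm that.

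Three narrower points stand:

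- A logistic model on dichotomised pressure could still test for some intervention effect. What it cannot do is estimate or test the mean difference in mmHg.
- The power figures ignore the repeated measures, the time effects and the cluster and individual correlations of a closed-cohort stepped wedge. The loss under the actual design cannot be computed from the article.
- The 140 mmHg cut, the control proportions and the 5% level are assumptions.

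**Conclusion.** The concern holds: the stated primary analysis is wrong for the stated primary outcome and must be corrected. This rests only on the article's own text and on the fact that a logistic model has no parameter in mmHg. It needs no assumption about SD, correlation or significance level.

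The size of the power loss is secondary and illustrative. From 90% on the mean, power falls to roughly 63–73% if systolic pressure is cut at 140 mmHg, under normality, independent observations, a two-sided 5% level, and the assumed range of means and SDs.

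**What to change.** In Data analysis, replace the sentence on the primary outcome with text along these lines:

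> Systolic blood pressure (mean of three readings, mmHg) at each 3-monthly occasion will be analysed with a linear mixed-effects model with fixed effects for measurement occasion and intervention, and random effects for cluster and individual. The result will be the adjusted mean difference in mmHg with its 95% confidence interval.

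Consequential edits:

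- State that mixed-effects logistic regression is for blood pressure control (below 140/90) and the other binary secondary outcomes, since the present cross-reference to the primary method would otherwise point to a linear model.
- State that continuous secondary outcomes use the same linear model as the primary outcome.
- Leave the sentence on duration of exposure in place; this change does not touch it.
- The section now describes time as a fixed effect at each step, whereas the abstract has the whole cohort measured every three months. The suggested text uses the measurement occasions. If the investigators mean the monthly steps, they should say so.

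The cost is a few sentences. No additional data are needed, and 869 need not change on this account, because it was already set for a mean difference. The change should be dated and made before outcome data are compared by intervention status.
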